### 5.2. Selection criteria:

Patients shall be assessed for the inclusion criteria at the time they are referred to the study clinic with a screening thick blood smear parasitaemia of > 2000/ul and < 200,000/ul. If the following criteria are met, patients will be enrolled in the study, assigned a study number, have blood removed by finger-prick for further laboratory tests (Giemsa-stained thick and thin blood smears, Hb measurement and blood collected on filter paper) and will be treated promptly according to their assigned antimalarial study regimen.

1. Age 6 months and above.
2. Fever (> 37.5ºC axillary) or history of fever in the previous 24 hours.
3. Absence of any history of serious side effects to study medications, including allergy to sulphonamide drugs
4. No evidence of a concomitant febrile illness which could interfere with the assessment of clinical treatment outcome
5. Provision of informed consent and ability to participate in 28-day follow-up (patient has easy access to health unit).
6. No history of treatment with an antifolate (sulfadoxine-pyrimethamine [single dose], metakelfin [single dose], TMP/Sulfa [> 3 days]) or amodiaquine (> 2 doses) during the last week (taking final dose within the 7 days prior to study enrolment).
7. Absence of pregnancy (menstruating women who have not missed their last menstrual period).
8. No danger signs or evidence of severe malaria defined as:

- Unarousable coma (if after convulsion, > 30 min)
- Repeated convulsions (> 2 within 24 h)
- Recent convulsions (1-2 within 24 h)
- Altered consciousness (confusion, delirium, psychosis, coma)
- Lethargy
- Unable to drink or breast feed
- Vomiting everything
- Unable to stand/sit due to weakness
- Severe anemia (Hb < 5.0 g/dL)
- Respiratory distress (laboured breathing at rest)
- Jaundice (yellow coloring of eyes)

Prior to the Day 1 return visit, the study laboratory technicians shall assess the results of the Giemsa-stained thick and thin blood smears. These shall not be available until after the patients have been treated and discharged from the clinic. Additional patients will be excluded from the study on Day 1 if they fail to meet the following additional inclusion criteria.

1. *P. falciparum* mono-infection
2. Parasite density > 2000/ul and < 200,000/ul.

Any patient who is excluded on Day 1 will be treated and followed-up in a clinically appropriate manner, but will not be followed for the 28-day period. The study number and treatment number of a patient excluded on Day 1 will not be re-assigned.

5.3. Process for obtaining informed consent:

Study clinicians shall conduct the screening interview and seek formal consent in the clinic. Once it has been determined that the subject meets the study entry criteria during the screening interview, all study details will be carefully discussed with the subject or their parents/guardian. All interviews shall be conducted in the native language of the patients and parents/guardians of children. Consent forms will be available in both English and the local language. Following the informed consent discussion, the patient or parents /guardians of children shall be asked to sign a written consent form. If they are unable to read and write, a fingerprint will be used in substitute for a signature and a witness will be asked to sign the form to document that the informed consent process was adequately conducted.

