### 5.0 PARTICIPANT SELECTION AND ENROLLMENT.

### 5.1. Recruitment and screening process:

Study subjects will be recruited from the OPD (outpatient department) of sentinel health centres. Patients who present with symptoms suggestive of malaria (fever or history of recent fever) will be referred to the outpatient laboratory/study laboratory for a screening thick blood smear (using standard Giemsa staining). Thick blood slides will be read and counted by the outpatient/study laboratory technicians. The parasite density of positive screening thick blood smears will be estimated by the outpatient laboratory technicians by counting the number of asexual parasites per 200 leukocytes, assuming a leukocyte count of 8,000/l. All patients who have a positive screening thick smear with a parasite density of > 2000/ul (>13 parasites per 200 leucocytes) and < 200,000/ul will be referred for further evaluation. After referral to the study clinic, the screening interview will take place. If the patient satisfies the selection criteria, they will be enrolled in the study. All patients who do not satisfy the selection criteria and are excluded from study enrolment will be referred back to the outpatient department for appropriate care.

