### 6.0 BASELINE EVALUATION AND TREATMENT ASSIGNMENT

### 6.1. Baseline evaluation and procedures:

On Day 0, patients enrolled and assigned study numbers will undergo a complete history and physical examination (Appendix 5 and 6). On day 0, a finger-prick blood sample will be obtained for repeat thick blood smear, thin blood smear, haemoglobin measurement and to save on filter paper for future molecular testing. Because only rapid Giemsa-stained thick smears are typically assessed in the outpatient laboratory, a thick and thin blood smear obtained at enrolment will be stained with 2% Giemsa and read by experienced laboratory technicians who are not involved in direct patient care. Parasite densities will be calculated by counting the number of asexual parasites per 200 leukocytes (or per 500, if the count is <10 parasites/200 leukocytes), assuming a leukocyte count of 8,000/l. A blood smear will be considered negative when the examination of 100 high power fields does not reveal asexual parasites. Gametocytemia will also be determined from thick smears. Thin smears will be used for parasite species identification.

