**Completion of Day 0 visit**

Baseline laboratory evaluations performed

Scheduled for follow-up on Days 1, 2, 3, 7, 14, 21, 28

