### APPENDIX 3. OUTCOME CLASSIFICATION

### Clinical Outcome Classification System

| ACR (Adequate Clinical Response)   - Absence of parasitemia on Day 28, without previously meeting criteria for ETF or LTF - Temperature < 37.5C (Axillary) and no history of fever in last 24 hours on day 28 irrespective of the presence of parasitemia, without previously meeting any of the criteria of ETF or LTF |
| --- |
| ETF (Early Treatment Failure): Days 0, 1, 2, and 3  - Development of danger signs or severe malaria on Days 0-3 in the presence of parasitemia - Parasitemia on Day 2 higher than Day 0 count irrespective of temperature - Temperature > 37.5C (Axillary) on Day 3 in presence of parasitemia - Parasitemia on Day 3 > 25% Day 0 count |
| LTF (Late Treatment Failure): Days 4 To 28  - Development of danger signs or severe malaria on Days 4 to 28 in the presence of parasitemia, without previously meeting any of the criteria of ETF. - Temperature > 37.5C (Axillary) or history of fever in last 24 hours on Days 4 to 28 in the presence of parasitemia, without previously meeting any of the criteria of ETF. |

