### APPENDIX 10. Adverse Event Reporting Guidelines

On Day 0 perform a careful history and physical exam and record your findings on the case record form (CRF), grading the patient reported symptoms and exam findings according to the guidelines presented in Appendices 3 and 4. Record the hemoglobin value and grade (Appendix 5) on the CRF as soon as they are available. All Day 0 values will serve as the patient’s baseline.

On all follow-up days, assess and grade the patient-reported symptoms and physical exam signs according to the guidelines in Appendices 3 and 4. Record the follow-up hemoglobin results obtained on Day 28 (and any extra day) and grade according to the guidelines in Appendix 5.

At each follow-up visit, evaluate the CFR for any reportable adverse events. Review for symptoms, physical exam signs, and hemoglobin results that are > grade 2 and are new or worsening by comparing the grade assigned on the follow-up day to the previous day’s record.

If a new or worsening symptom, sign, or laboratory value is present (increasing grade compared to the previous day’s value and > grade 2), answer “YES” in the appropriate column for reporting adverse events on the CRF (otherwise, answer “NO”).

An adverse event is defined as any “untoward” (unfavorable or undesirable) medical occurrence in a patient who has received a medication that may or may not be related to this treatment. Any event (patient-reported symptom, physical exam finding, or laboratory value) that occurs after treatment with a study medication that is new or worsening from Day 0 should be considered a possible adverse event, regardless of whether you think that the treatment caused the event.

The following scenarios are examples of adverse events (AEs):

|  | **Day 0** | **Day 1** | **Day 2** |
| --- | --- | --- | --- |
| Nausea | 0 | 0 | 2 |

AE = nausea on Day 2

|  | **Day 0** | **Day 1** | **Day 2** | **Day 3** |
| --- | --- | --- | --- | --- |
| Nausea | 2 | 1 | 0 | 2 |

AE = nausea on Day 3

For each new / worsening event of > grade 2, the following information will be collected on the Adverse Event Record Form:

1. Description of event
2. Date of event onset
3. Date event reported
4. Maximum severity of the event
5. Maximum suspected relationship of the event to study medication
6. Is the event serious?
7. Initials of the person reporting the event
8. Was the event episodic or intermittent in nature?
9. Outcome
10. Date event resolved

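### Hb < 5.0 g/dL bars entry, but Hb is sampled only once the criteria are judged met; no result is required before allocation, and a low Day 0 value has two conflicting statuses

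*Protocol*

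**What the plan says.** **The criterion.** Section 5.2 lists, among the danger signs and severe-malaria features that bar entry, "Severe anemia (Hb < 5.0 g/dL"). Appendix 13 repeats it as a criterion for severe malaria. The Appendix 8 screening form carries it in item 8, an immediate screening item; only species and parasite density are marked for completion by the Day 1 visit.

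**What is measured before enrolment.** Under section 5.1, patients with suggestive symptoms "will be referred to the outpatient laboratory/study laboratory for a screening thick blood smear". No haemoglobin test is mentioned at that stage. Section 5.3 has the clinician settle eligibility in the screening interview, before the consent discussion.

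**When Hb is taken.** Section 5.2: "If the following criteria are met, patients will be enrolled in the study, assigned a study number, have blood removed by finger-prick". The same sentence names the tests, Hb among them: once enrolled, patients "have blood removed by finger-prick for further laboratory tests (Giemsa-stained thick and thin blood smears, Hb measurement and blood collected on filter paper"). Section 6.1, on patients who are already enrolled and numbered: "On day 0, a finger-prick blood sample will be obtained for repeat thick blood smear, thin blood smear, haemoglobin measurement". Appendix 1 shows clinical evaluations at initial enrolment, then randomisation and dosing, and then a box for completing the Day 0 visit that reads "Baseline laboratory evaluations performed". Appendix 10 says: "Record the hemoglobin value and grade (Appendix 5) on the CRF as soon as they are available".

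**What happens to a low value.** The Day 1 exclusions in section 5.2 cover species and parasite density. The post-enrolment exclusions that follow section 7.3 cover other antimalarials, concomitant febrile illness and withdrawal of consent, and the case record form offers the same three reasons. Appendix 3 includes in early treatment failure (ETF): "Development of danger signs or severe malaria on Days 0-3 in the presence of parasitemia". The case record form has a matching tick box. Section 8.2 limits the primary population to randomised patients who met the entry criteria.

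**The concern.** A numeric entry threshold can be applied only if the number exists when eligibility is decided. As sequenced here, the clinician must certify that Hb is not below 5.0 g/dL before the sample is drawn. The exclusion therefore cannot do its work at the point where the protocol places it.

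The second difficulty affects the primary endpoint. If the value turns out to be below 5.0 after enrolment, one part of the protocol can be read as making the patient a clinical failure, and another as removing the patient from the primary analysis. The first choice would score a pre-treatment state as drug failure and add failures unrelated to treatment to every arm. The second would remove patients after randomisation. Left open, the choice may be made differently at different sites or after results are seen. Classification as ETF also triggers rescue treatment under section 7.3, so the ambiguity reaches beyond the analysis.

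**Working it through.** **1. Order of events, side by side.**

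- Section 5.1: the thick smear is the only blood test before referral to the study clinic.
- Section 5.2: criteria met, enrolled, study number, finger-prick with Hb, then treatment.
- Section 6.1: Hb on Day 0 in patients already enrolled.
- Section 4.4: unspecified baseline evaluations by the clinicians, then referral to the nurse for allocation. Hb is not named.
- Appendix 1: clinical evaluations, randomisation and first dose, then laboratory evaluations. The chart's arrows are not in the text reviewed, so this order is inferred from the sequence of boxes.
- Appendix 10: Hb recorded when available, with no time limit.

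Every passage that names Hb puts it after the eligibility decision. Whether it falls before or after allocation is not fixed: Appendix 1 suggests after, while sections 4.4 and 5.2 allow before. No passage makes the result a condition of allocation.

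**2. Routes for a Day 0 Hb < 5.0 found after enrolment.** Day 1 exclusion: not listed. Post-enrolment exclusion: not listed. Case record form exclusion reasons: not listed. ETF: Appendix 13 makes it severe malaria, and Appendix 3 and the form count severe malaria on Days 0-3 with parasitaemia. Section 8.2: criterion 8 is not met, so the patient is outside the primary population. The last two conflict.

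**3. The plan's sample size (section 8.1).** Inputs: two-sided alpha 0.05, power 80%, 15% vs 5% and 10% vs 2%. With d = p1 − p2 and p̄ their mean:

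n′ = [1.96√(2p̄(1−p̄)) + 0.8416√(p1(1−p1)+p2(1−p2))]² / d²

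n = (n′/4)[1 + √(1 + 4/(n′d))]²

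- 15% vs 5%: n′ = 140.1, n = 159.5, rounded up to 160.
- 10% vs 2%: n′ = 137.2, n = 161.2, rounded up to 162.

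These match the stated 160 and 162, so the plan used the continuity correction. For 10% loss, 160/0.9 = 178 and 162/0.9 = 180, against 180 stated for both.

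**4. If low-Hb patients are counted as failures.** Let h be the share of randomised patients with Day 0 Hb < 5.0. The protocol gives no value; 0.5% to 3% is an assumption (0.9 to 5.4 patients per group of 180). Each failure rate becomes p′ = p(1−h) + h, so the risk difference becomes (1−h)d. Corrected power uses n′ = (nd−1)²/(nd²) in the first formula, solved for power, at n = 160 and 162.

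| h | Rates | Risk difference | Risk ratio | Power, corrected | Power, uncorrected |
|---|---|---|---|---|---|
| 0 | 10% vs 2% | 8.0 points | 5.0 | 80% | 86% |
| 0.5% | 10.5% vs 2.5% | 8.0 | 4.2 | 77% | 83% |
| 3% | 12.7% vs 4.9% | 7.8 | 2.6 | 62% | 69% |
| 0 | 15% vs 5% | 10.0 | 3.0 | 80% | 85% |
| 0.5% | 15.4% vs 5.5% | 10.0 | 2.8 | 78% | 83% |
| 3% | 17.6% vs 7.9% | 9.7 | 2.2 | 69% | 74% |

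Worked row (10% vs 2%, h = 3%): d = 0.0776; n′ = (162 × 0.0776 − 1)²/(162 × 0.0776²) = 137.25; z = (0.909 − 0.786)/0.397 = 0.31; power 62%.

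**5. If they are omitted under section 8.2.** The rates stay as planned and n becomes n(1−h). At h = 3%, corrected power is 78.8% in both scenarios (from 80.2% and 80.1%). Uncorrected, it is 85.1% (from 86.2%) and 83.9% (from 85.0%).

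**The case against.** **Patients may not yet be randomised when Hb is known.** A reader might infer that severely anaemic patients are necessarily randomised and dosed. The documents do not establish that. Section 4.4 places baseline evaluations before referral to the nurse, and the step order in section 5.2 puts the finger-prick before treatment. The statement that results arrive only after discharge concerns the smears, not Hb. The support for Hb after dosing is the box order in Appendix 1. This objection stands against the stronger reading. It does not rescue the sequence, because eligibility is still decided before Hb is taken and no result is required before allocation.

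**An exclusion route exists.** The screening form tells staff to exclude a patient with any disqualifying response and stays open until Day 1 for two items. Appendix 1 has an exclusion box that reassigns the study number, so some exclusion after numbering was foreseen. In part this stands. But the Hb item is not among those left open, and neither the Day 1 list nor the later exclusion lists mention it.

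**The patient does have a classification.** A reader might infer that such a patient has no valid classification at all. That goes too far: section 8.2 is a written rule that would leave the patient out of the primary analysis. The ETF reading is also strained, because the criterion speaks of development and a pre-dose value has not developed on treatment. Still, nothing in Appendix 3 or on the form exempts a condition already present on Day 0, so the two readings remain in conflict.

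**The power figures are conditional.** This stands. They need both an assumed frequency and the ETF reading. The summary measure in section 8.2 is a risk difference, which hardly moves.

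**Conclusion.** The point holds as a sequencing contradiction with an unresolved consequence for the primary endpoint. The protocol applies an Hb threshold before Hb is measured, does not require the result before allocation, and leaves a Day 0 value below 5.0 with two incompatible statuses. None of this depends on a figure.

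The size is unknown, because the frequency of Hb < 5.0 among otherwise eligible patients is not in the documents. Under an assumed 0.5% to 3%, with all such patients counted as failures and equally frequent in each arm, power on the plan's own basis falls from 80% to 77%-62% (10% vs 2%) or 78%-69% (15% vs 5%). The loss comes mainly from the higher variance at higher failure rates; the risk difference shrinks by 0.3 points at most. If the patients are omitted instead, power falls by about 1.5 points or less. A reader might take the larger loss as a demonstrated defect of the sample size. It is not: it arises on one of two readings and at an assumed frequency.

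The point is worth correcting because the remedy is cheap and the exclusion is a safety criterion.

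**What to change.** 1. In sections 5.2 and 6.1 and Appendix 1, state that Hb from the existing Day 0 finger-prick is read after consent and before the nurse assigns a treatment number. The protocol's own criterion can then be applied before randomisation. Section 5.3 and item 8 of the screening form need the matching change, since eligibility on Hb would be settled after consent.
2. Reconcile the selection criteria and Day 1 exclusions (section 5.2), the post-enrolment exclusions (after section 7.3), the primary population (section 8.2), the ETF definition (Appendix 3) and the case record form, so that a pre-dose Day 0 Hb below 5.0 has one stated status in the primary analysis. Because ETF also governs rescue treatment, the investigators must settle the clinical side; no rule is proposed here.

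Cost: no extra test or blood draw. There is a wait on Day 0 for the Hb reading, whose length cannot be given because the protocol states neither method nor turnaround. Some patients will consent and then be found ineligible before allocation. The second item is a change of text and forms only.

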### 6.0 BASELINE EVALUATION AND TREATMENT ASSIGNMENT

### 6.1. Baseline evaluation and procedures:

On Day 0, patients enrolled and assigned study numbers will undergo a complete history and physical examination (Appendix 5 and 6). On day 0, a finger-prick blood sample will be obtained for repeat thick blood smear, thin blood smear, haemoglobin measurement and to save on filter paper for future molecular testing. Because only rapid Giemsa-stained thick smears are typically assessed in the outpatient laboratory, a thick and thin blood smear obtained at enrolment will be stained with 2% Giemsa and read by experienced laboratory technicians who are not involved in direct patient care. Parasite densities will be calculated by counting the number of asexual parasites per 200 leukocytes (or per 500, if the count is <10 parasites/200 leukocytes), assuming a leukocyte count of 8,000/l. A blood smear will be considered negative when the examination of 100 high power fields does not reveal asexual parasites. Gametocytemia will also be determined from thick smears. Thin smears will be used for parasite species identification.

### 6.2. Treatment group assignment:

At the time of enrolment, patients will be randomly assigned to one of the treatment groups. Randomisation shall be according to a pre-determined randomisation list stratified by age. Treatment allocation and administration of medications will be done by the study nurse who will not be involved in outcome classification and will remain the only member of the study team not blinded to the treatment groups.

Administration of study medications will be performed by the study nurse and will be directly observed (Appendix 4). Any patient who vomits the medication within 30 minutes of administration of the drugs will be retreated with a second dose. If the patient vomits repeatedly on Day 0, and is unable to retain the dose of the study medication, the patient will be excluded from the study.If this occurs on Days 1 or 2, the patient will be classified as a treatment failure, referred for appropriate care and treated with parenteral antimalarial medication.

Patients will receive acetaminophen 10 mg/kg with instructions to take it every 8 hours until the resolution of fever. Any child with a hemoglobin of < 10.0 gm/dl will be treated with iron sulfate for 2 weeks and mebendazole (only those aged 1 - 5 years).

### 6.3. Study drug information:

### 6.3.1 Study drug formulation and labeling:

| **Drug** | **Trade name**  **Manufacturer** | **Class** |
| --- | --- | --- |
| Amodiaquine (200mg) | Camoquin  Parke-Davis | 4-aminoquinoline |
| Artesunate (50mg) | Arsumax  Sanofi/Winthrop | Artemisinin derivative |
| Chloroquine (250 mg) | Cosmoquin  Cosmos, Kenya | 4-aminoquinoline |
| Sulfadoxine-pyrimethamine  (500mg/25mg) | Fansidar  Roche | Antifolate combination |

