### 4.4. Treatment allocation and masking:

On the day of enrolment, study participants will undergo baseline evaluations and be assigned a study number by the clinicians. Patients will then be referred to the study nurse who will be responsible for the treatment group assignment and allocation of the study medications. The study nurse will note the patient’s age and select the next available treatment number and corresponding assigned treatment. The study nurse will record directly onto the randomization list the date and time of treatment assignment and study number. Once a month, a copy of the updated randomization list will be placed by the study nurse into sealed envelopes and delivered to the administrative office in Kampala where they will be stored securely. The original randomization list will be crosschecked to assure adherence to the randomisation code. Initial studies will involve one of the two following treatment comparison designs:

1. Two-arm study – CQ/SP vs. AQ/SP
2. Three-arm study - CQ/SP vs. AQ/SP vs. AQ/AS

Sentinel sites with previously identified low levels of drug resistance and/or lower-level capacity for the conduct of complex studies will be chosen for the two-arm study. Sentinel sites with previously identified higher levels of drug resistance and greater capacity will be chosen for the three-arm study.

The nurse shall administer study medications according to weight-based guidelines (Appendix 4). Study medications will not be identical in appearance or taste, however other procedures will be followed in an attempt to mask the patients to their treatment. Patients will not be informed of their treatment regimen and identical dosing regimens will be used in all the treatment arms. In studies where AS/AQ shall be compared with CQ/SP and AQ/SP, patients assigned to CQ/SP and AQ/SP shall be given a placebo (lactose tablets) on day 1 and day 2 in the same amount as AS. Administration of study medications will be directly observed. Any patient who vomits the medication within 30 minutes of administration of the drugs will be retreated with a second dose. If the patient vomits repeatedly on Day 0, they shall be excluded. If the patient vomits repeatedly on Day 1 or 2 and is unable to retain the dose of the study medication, the patient will be classified as a treatment failure and referred for appropriate care with parental antimalarial medication.

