### 6.3.2 Study drug dosing schedule:

| **Treatment Groups** | **Medications** | **Day 0** | **Day 1** | **Day 2** |
| --- | --- | --- | --- | --- |
| CQ/SP | CQ | 10 mg/kg | 10 mg/kg | 5 mg/kg |
| SP | 25 mg/kg sulfa component | Placebo if 3-arm  study | Placebo if 3-arm  study |
| AQ/SP | AQ | 10 mg/kg | 10 mg/kg | 5 mg/kg |
| SP | 25 mg/kg sulfa component | Placebo if 3-arm  study | Placebo if 3-arm  study |
| AS/AQ | AS | 4 mg/kg | 4 mg/kg | 4 mg/kg |
| AQ | 10 mg/kg | 10 mg/kg | 5 mg/kg |

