### APPENDIX 4. WEIGHT-BASED ADMINISTRATION OF STUDY MEDICATIONS

**Weight-Based Administration of Study Medications (2-arm study)**

| **Weight (kg)** | **Amodiaquine (AQ)**  **200 mg tabs** | | | **Chloroquine (CQ)**  **250 mg tabs** | | | **SP (500mg/**  **25 mg)** |
| --- | --- | --- | --- | --- | --- | --- | --- |
|  | **Day 0** | **Day 1** | **Day 2** | **Day 0** | **Day 1** | **Day 2** | **Day 0** |
| 5 | ¼ | ¼ | ¼ | ¼ | ¼ | ¼ | ¼ |
| 6 | ¼ | ¼ | ¼ | ½ | ¼ | ¼ | ¼ |
| 7 | ¼ | ¼ | ¼ | ½ | ½ | ¼ | ¼ |
| 8 | ½ | ¼ | ¼ | ½ | ½ | ½ | ½ |
| 9 | ½ | ¼ | ¼ | ½ | ½ | ½ | ½ |
| 10 | ½ | ½ | ¼ | ¾ | ½ | ½ | ½ |
| 11 | ½ | ½ | ¼ | ¾ | ¾ | ½ | ½ |
| 12 | ½ | ½ | ½ | ¾ | ¾ | ½ | ½ |
| 13 | ½ | ½ | ½ | 1 | ¾ | ½ | ¾ |
| 14 | ¾ | ½ | ½ | 1 | 1 | ½ | ¾ |
| 15 | ¾ | ½ | ½ | 1 | 1 | ½ | ¾ |
| 16 | ¾ | ¾ | ½ | 1 | 1 | ¾ | ¾ |
| 17 | ¾ | ¾ | ½ | 1 | 1 | 1 | ¾ |
| 18 | 1 | ¾ | ½ | 1 | 1 | 1 | ¾ |
| 19 | 1 | ¾ | ½ | 1 ¼ | 1 | 1 | 1 |
| 20 | 1 | 1 | ½ | 1 ¼ | 1 ¼ | 1 | 1 |
| 21 | 1 | 1 | ½ | 1 ¼ | 1 ¼ | 1 | 1 |
| 22 | 1 ¼ | 1 | ½ | 1 ½ | 1 ½ | ¾ | 1 |
| 23 | 1 ¼ | 1 | ½ | 1 ½ | 1 ½ | 1 | 1 ¼ |
| 24 | 1 ¼ | 1 ¼ | ½ | 1 ½ | 1 ½ | 1 | 1 ¼ |
| 25 | 1 ¼ | 1 ¼ | ½ | 1 ½ | 1 ½ | 1 ¼ | 1 ¼ |
| 26-27 | 1 ¼ | 1 | 1 | 1 ½ | 1 ½ | 1 ¼ | 1 ½ |
| 28 | 1 ¼ | 1 ¼ | 1 | 2 | 1 ½ | 1 ½ | 1 ½ |
| 29-31 | 1 ¼ | 1 ¼ | 1 | 2 | 2 | 1 | 1 ½ |
| 32 | 1 ½ | 1 ½ | 1 | 2 | 2 | 1 ½ | 1 ½ |
| 33 | 1 ½ | 1 ½ | 1 | 2 | 2 | 1 ½ | 1 ½ |
| 34-35 | 1 ½ | 1 ½ | 1 ¼ | 2 | 2 | 2 | 1 ½ |
| 36-37 | 1 ½ | 1 ½ | 1 ¼ | 2 | 2 | 2 | 1 ½ |
| 38 | 2 | 1 ½ | 1 ¼ | 2 | 2 | 2 | 2 |
| 39 | 2 | 1 ½ | 1 ¼ | 2 | 2 | 2 | 2 |
| 40-43 | 2 | 2 | 1 | 2 ½ | 2 ½ | 1 ½ | 2 |
| 44-47 | 2 | 2 | 1 ½ | 3 | 3 | 2 | 2 ½ |
| 48-49 | 2 | 2 | 2 | 3 | 3 | 2 | 2 ½ |
| 50-59 | 2 ½ | 2 | 2 | 4 | 4 | 2 | 2 ¾ |
| >60 | 3 | 3 | 1 ½ | 4 | 4 | 2 | 3 |

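### At the labelled 250 mg per tablet, the Appendix 4 chloroquine counts give 37.5 to 50.0 mg/kg in total for 5 to 60 kg, against 25 mg/kg in section 6.3.2; the basis of the milligrams is not stated

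*Protocol*

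**What the plan says.** The protocol gives three figures for chloroquine.

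- **Strength.** Section 6.3.1 lists "Chloroquine (250 mg" with a trade name and manufacturer. The chloroquine column headers in both Appendix 4 tables also give 250 mg tablets.
- **Target.** Section 6.3.2 gives the daily doses as "CQ/SP | CQ | 10 mg/kg | 10 mg/kg | 5 mg/kg" for Days 0, 1 and 2.
- **Tablet counts.** Appendix 4 gives tablets by weight. In the two-arm table, columns 1 to 3 after the weight are amodiaquine, columns 4 to 6 chloroquine and column 7 SP. The lowest row reads "5 | ¼ | ¼ | ¼ | ¼ | ¼ | ¼ | ¼", the second-highest "50-59 | 2 ½ | 2 | 2 | 4 | 4 | 2 | 2 ¾" and the open-ended top row ">60 | 3 | 3 | 1 ½ | 4 | 4 | 2 | 3". The chloroquine columns of the three-arm table are the same.

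Section 4.4 states the administration rule: "The nurse shall administer study medications according to weight-based guidelines (Appendix 4"). Section 6.2 refers to the same appendix. Nowhere does the protocol say whether the 250 mg or the mg/kg target refers to salt or base. For SP, by contrast, section 6.3.2 does name the component in which the dose is expressed.

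**The concern.** Target, strength and count are tied by simple arithmetic: counts times strength, divided by weight, should return the target up to tablet-fraction rounding. For chloroquine they do not.

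Chloroquine plus SP is the reference arm in both designs (section 4.4) and in the study aim (section 3.0), and enrolment starts at 6 months of age (section 5.2). Anyone who checks a dose, audits adherence, replaces a supply or reports the regimen from sections 6.3.1 and 6.3.2 will get a different number of tablets from the one that Appendix 4 tells the nurse to give. At 50 kg the two sections imply 25 × 50 / 250 = 5 tablets, and Appendix 4 gives 10. At 10 kg they imply 25 × 10 / 250 = 1 tablet, and Appendix 4 gives 1¾.

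**Working it through.** **Inputs.** Chloroquine target 10 + 10 + 5 = 25 mg/kg (6.3.2). Tablet strength 250 mg (6.3.1 and Appendix 4 headers). Tablets per day from Appendix 4. For comparison, amodiaquine 200 mg with the same 10, 10 and 5 mg/kg target, and SP with 500 mg sulfadoxine per tablet and a target of 25 mg/kg of that component.

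**Formula.** Total mg/kg = (Day 0 + Day 1 + Day 2 tablets) × strength / weight, for every whole kilogram from 5 to 60.

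**Step 1: check of the method on the other drugs.** At 10 kg, amodiaquine gives (½ + ½ + ¼) × 200 / 10 = 25.0 mg/kg and sulfadoxine ½ × 500 / 10 = 25.0 mg/kg. Across 5 to 60 kg, amodiaquine runs from 21.4 to 30.0 (mean 24.2) and sulfadoxine from 17.9 to 31.3 (mean 24.8). Both centre on 25, so the table is read correctly and rounding averages out.

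**Step 2: chloroquine at the labelled 250 mg.**

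| Weight (kg) | Tablets, Days 0–2 | Total mg/kg | Ratio to 25 |
| --- | --- | --- | --- |
| 5 | 0.75 | 0.75 × 250 / 5 = 37.5 | 1.50 |
| 8 | 1.5 | 1.5 × 250 / 8 = 46.9 | 1.88 |
| 10 | 1.75 | 1.75 × 250 / 10 = 43.8 | 1.75 |
| 20 | 3.5 | 3.5 × 250 / 20 = 43.8 | 1.75 |
| 50 | 10 | 10 × 250 / 50 = 50.0 | 2.00 |
| 60 | 10 | 10 × 250 / 60 = 41.7 | 1.67 |

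Over all 56 weights the minimum is 37.5, the maximum 50.0 and the mean 42.8 mg/kg (42.8 / 25 = 1.71). The stated 25 mg/kg is not reproduced at any of them. On Day 0 alone the dose runs from 12.5 mg/kg (5 kg: ¼ × 250 / 5) to 20.8 mg/kg (6 kg: ½ × 250 / 6), against 10.

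**Step 3: the open-ended top row.** Above 60 kg the count stays at 10 tablets, so the total is 2500 / weight. It falls below 37.5 mg/kg above 2500 / 37.5 = 66.7 kg, and is 35.7 at 70 kg, 31.3 at 80 kg and 25.0 at 100 kg. The range of 37.5 to 50.0 therefore holds for 5 to 60 kg only.

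**Step 4: what strength would restore the target.** Solving 25 × weight / tablets gives 125 to 167 mg per tablet (mean 146). If 150 mg is assumed, the totals run from 22.5 to 30.0 mg/kg (mean 25.7) and are exactly 25.0 at 12 of the 56 weights. The 150 mg is an assumption and appears nowhere in the protocol.

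**Step 5: individual days under that assumption.** Day 2 would run from 4.8 mg/kg (31 kg: 1 × 150 / 31) to 9.4 mg/kg (8 kg: ½ × 150 / 8), against 5. At 17 kg it would be 1 × 150 / 17 = 8.8. Totals that centre on 25 do not make each day agree with 10, 10 and 5.

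**The case against.** The strongest reply is that nothing is left open at the point of care. Sections 4.4 and 6.2 make Appendix 4 the rule, one nurse gives the drug under direct observation, section 6.3.1 names the product, and both tables carry the same chloroquine counts. No passage tells staff to calculate from mg/kg. This stands. A reader might infer that the control-arm dose is undefined, or that both treatment contrasts hang on which passage is followed. The protocol does not support that: a site that follows Appendix 4 gives the same tablets at each weight as any other.

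The second reply is that the pattern looks like a labelling gap, such as salt against base, rather than a faulty table. The mean excess of 1.71 is close to 250 / 150 = 1.67, and the spread under 150 mg (22.5 to 30.0) is much like that of amodiaquine (21.4 to 30.0). This also stands as a plausible explanation. A reader might infer from the ratio of 1.5 to 2.0 that children receive up to twice the intended dose. That is not shown.

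Neither reply removes the conflict. The explanation has to be supplied from outside the protocol, and the note under Appendix 12 records that the package insert for the named chloroquine product was not available.

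**Conclusion.** The labelled strength, the mg/kg target and the tablet counts for chloroquine cannot all hold as written, and no other passage reconciles them. The size is 37.5 to 50.0 mg/kg against 25 mg/kg for 5 to 60 kg, taking 250 mg as the quantity dosed. What is undefined is the basis of the milligrams; the number of tablets is fixed. Whether the explanation is an unstated basis or an error in one of the three places cannot be settled from the protocol, and no view is taken here on which figure is right. The point needs resolving because it concerns the reference drug of every comparison in a trial that enrols infants, and the repair is cheap.

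**What to change.** Reconcile section 6.3.1, section 6.3.2 and both Appendix 4 tables. State the quantity in which the chloroquine mg/kg target is expressed, and give the tablet content in that same quantity in 6.3.1 and in the Appendix 4 headers. Then recheck every chloroquine row against the target, day by day as well as in total, including the open-ended top row. The clinical team decides which figure stands.

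The cost is a short protocol amendment and, if any row changes, a re-issued dosing card. This reconciliation does not touch the randomisation or the analysis plan.
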